**Study design:**

The proposed study will be a four-group randomised control trial (RCT) design, with equal allocation of participants to the three intervention groups and one control group.

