### Sample size calculation

Previous study [13, 14] showed physical exercise had notable effects (corresponding to a Cohen’s *d* of about 0.9) on improving sleep onset latency, sleep duration and sleep duration. We assumed that melatonin supplements have similar effects on sleep. A sample of 20 participants per group is computed by G*power software to achieve a power of 80% and a level of significance of 5% and 95% confidence level. Assuming 25% attrition rate, 25 participants per group will be recruited (i.e. the total number is 100).

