### Randomization

Participants will be randomly assigned to three intervention groups or a placebo-control group by a trained research staff using MS Excel randomization function. Block randomization with block size of 5 will be used for equal allocation ratios.

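### A block size of 5 is incompatible with the equal four-arm allocation it is meant to provide, so 25 per arm is not ensured

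*Protocol article*

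**What the plan says.** The Abstract (Study design) of the protocol article describes a four-group trial "with equal allocation of participants to the three intervention groups and one control group". The Randomization section repeats the four arms ("Participants will be randomly assigned to three intervention groups or a placebo-control group") and then gives the mechanism: "Block randomization with block size of 5 will be used for equal allocation ratios". The list is to be produced by a trained staff member with a spreadsheet randomisation function.

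The Sample size calculation section gives the target: "25 participants per group will be recruited (i.e. the total number is 100" children. That figure is the recruitment number after an allowance for attrition. The power calculation itself rests on 20 per group.

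The article does not say how the fifth place in a block is filled, whether it rotates between arms, or whether 5 means five places per arm.

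**The concern.** The block size and its stated purpose stand in one sentence and contradict each other. This is not a detail that the article leaves to a fuller document: a specific number is given, and it does not fit a four-arm design with equal allocation.

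Two things are at stake. First, the planned 25 per arm is no longer a consequence of the randomisation scheme. It depends on how the odd place in each block is handled. Second, the sequence cannot be reproduced from the protocol, because a rule for the fifth place has to come from somewhere and none is given in the article. How much harm follows depends on that unstated rule.

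**Working it through.** **Inputs from the protocol article**
- Arms: 4 (Abstract, Study design; Randomization).
- Block size: 5 (Randomization).
- Recruitment: 25 per arm, 100 in total (Sample size calculation).
- Effect size d: about 0.9; power 80%; significance level 5%; 20 per group; attrition 25% (Sample size calculation). Sidedness is not stated; two-sided is assumed here.

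**1. The plan's own sample size.** By the normal approximation, n per group = 2 × (1.960 + 0.842)² / 0.9² = 19.4, rounded up to 20. This matches "A sample of 20 participants per group is computed by G*power software". The exact t-test gives 79.2% power at 20 per group and 81.2% at 21, which is close enough to count as reproduced. The recruitment figure follows as 20 × 1.25 = 25. None of this depends on the block size.

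**2. Divisibility.** 5 / 4 = 1.25 places per arm. No block of 5 can hold four arms equally; the nearest is 2:1:1:1. The number of blocks is 100 / 5 = 20.

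**3. Final arm sizes if the fifth place is drawn at random in each block (assumption).** Each block gives every arm one place, plus one extra place to an arm chosen with probability 1/4. The four arm sizes are then 20 plus a multinomial count (20 draws, probability 1/4 each).
- Expected size of an arm: 20 + 20 × 1/4 = 25.
- Standard deviation of an arm: √(20 × 0.25 × 0.75) = 1.94.
- Chance of exactly 25 in every arm: 20! / (5!)⁴ / 4²⁰ = 0.0107, or 1.1%.
- By enumerating all outcomes: mean gap between largest and smallest arm 4.6 children; chance of a gap of 4 or more 69%.

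**4. Final arm sizes under other rules for the fifth place**

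| Rule for the fifth place | Result at 100 children |
|---|---|
| Random in each block | about 25 per arm, not exact (step 3) |
| Always the same arm | 20 + 20 = 40 in that arm, 20 in each of the others |
| Forced to rotate, 5 blocks per arm | 25 per arm, but in effect a block of 20 |

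**5. Effect on power (two-sided t-test at 5%, d = 0.9).** Each arm is reduced in the plan's own proportion of 25 recruited to 20 evaluable, a factor of 0.8.
- Equal arms, 20 v 20: 79.2%.
- An uneven pair, 22 v 18: 78.8%.
- Random fifth place, averaged over outcomes for a given pair of arms: 79.0%.
- Random fifth place, the two smallest arms each time: 76.5% on average.
- Two of the smaller arms in a 40/20/20/20 split, 20 × 0.8 = 16 v 16: 69.3%.

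**6. Block sizes that work.** The multiples of 4 below 100 that also divide 100 are 4 and 20. Blocks of 4: 100 / 4 = 25 blocks and exactly 25 per arm. Blocks of 20: 5 blocks and exactly 25 per arm. If each block is 4 or 8 with equal chance and nothing else is fixed, a block ends exactly at child 100 with probability about 2/3. Otherwise the last block of 8 is cut in half and the arms may differ.

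**The case against.** The strongest defence is that little harm follows in the plausible case. With a random fifth place every child still has a 1/4 chance of each arm, the expected ratio is 1:1:1:1, the comparison is not biased, and average power for a pair of arms falls by about 0.2 percentage points (79.2% to 79.0%). In 20 complete blocks of at best 2:1:1:1, no arm receives fewer than 20 children. The power calculation rests on 20 evaluable per arm, not on 25 recruited. All of this stands.

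It can also be said that 5 was meant as five per arm, or that the extra place rotates equally. Either would give exactly 25 per arm. Neither is written, and in both cases the effective block is 20, so the sentence would still need correcting.

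A reader might go further and infer that equal allocation will not be delivered, or that the trial is heading for 40/20/20/20. The documents do not support either. Exact equality remains possible, and equality in expectation holds if the fifth place is random. The uneven split needs the extra place to go to one arm every time, which the article does not say. Nor does it follow that staff will improvise the rule: a fuller protocol may specify the algorithm. That document could explain the number, but it could not make a block of 5 balanced over four arms.

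**Conclusion.** The point holds as an internal contradiction. A block size of 5 cannot give the balance over four arms that the same sentence claims for it, and no other section repairs it. What is lost is the assurance of 25 per arm, not the equal ratio in expectation.

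Under the assumption of a randomly filled fifth place, exact balance is unlikely but the typical imbalance is a few children, and the effect on power is minor. That figure assumes d = 0.9, a two-sided 5% test and the plan's own 25-to-20 loss. The fall to about 69% power between two of the smaller arms is an adverse bound that rests on an unstated rule. It is not a prediction. The correction is worth requiring because it costs almost nothing and has to be in place before allocation begins.

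**What to change.** In the Randomization section, replace the block size of 5 with a multiple of 4. Three forms would meet the stated aim:
- fixed blocks of 4, which give 25 blocks and exactly 25 children per arm;
- blocks randomly varied between 4 and 8, with the list constrained to total 100, since without that constraint the last block may be left incomplete;
- a block size of 20, stated as such, if five places per arm was the intention.

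Generate the list before the first child is randomised. The cost is one corrected sentence and one regenerated list; no further participants or staff are needed, and the sample-size calculation does not change.

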### Patient and public involvement

Patients and public will not be involved in the study.

### Blinding

The person analysing the sleep parameters and melatonin level will be blinded for the group assignment.

### Ethical considerations

Prior to the study, information about the study were provided to all participants and their parents. Written consent and verbal assent were obtained from them. All data were encrypted with passwords and only the authors could access to the data. Ethical approval was obtained from the first author’s institution (Reference no: 2019-2020-0470). The results of the study will be published in a peer-reviewed journal. Findings of the study will also be shared with other university and non-governmental organisations in Hong Kong that specialise in autism by means of a formal dissemination webinar. The trial registration number is NCT04878198 from https://clinicaltrials.gov/.

### Statistical methods

All statistical analyses will be conducted using SPSS (version 26.0) for Windows (SPSS Inc., Chicago, IL, USA). All the data will be entered into SPSS by the research assistant. One-way (4 Groups: physical exercise vs melatonin supplement vs combined exercise and melatonin supplement vs placebo-control) analysis of variances (ANOVA) with repeated measures will be performed to compare changes in actigraphy data and endogenous melatonin level between and within groups over different time points (i.e. T1-T3). Post-hoc analyses will be performed when any significant difference both between- and within-group is found in any of the outcome variables. Bonferroni correction will be used to adjust the alpha levels. Depending on the proportion of missing data and the assumption of normality, multilevel regression or a generalized estimating equation (GEE) will also be used as a sensitive analysis to assess the effects of the physical exercise intervention, melatonin supplement, time effect, and their interaction with sleep outcomes and melatonin level outcomes if there is any missing data. Average time spent in both daily sedentary activity and MVPA at baseline will be used as covariates. Linear regression will be used to analyse the association between participant’s adherence to the intervention and the outcome variables as a secondary analysis. Mediation analysis will be conducted to examine the mediating effect of endogenous melatonin level at T2 on the relation between physical exercise and sleep at T3. Preacher and Hayes’ bootstrapping and conditional process modeling will be used to determine the significance of the mediating effect. A p-value of <0.05 will be considered statistically significant. Both proposal analysis and intention-to-treat analysis will be carried out. Demographic variables (e.g. age, sex, BMI) will be adjusted if they demonstrate clinically significant prognostic effects on the outcomes (with absolute correlation or Cohen’s d effect size of >0.2) for both main analysis and mediation analysis.

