### Intervention

Each participant will attend 3 one-week-long assessments in their respective schools, where we will assess their habitual sleep patterns and endogenous melatonin level before the intervention (T1), in the mid of the study (5 weeks after the commencement of the study) (T2) and after the 10-week intervention (T3). The mid-assessment is valuable to know how much variance in sleep behaviors is accounted by variance in melatonin, as well as to assess the adherence of the interventions. SPIRIT schedule of the study and a flow diagram of the study are shown in Figs 1 and 2 respectively. The estimated starting date of the study will be 1^st^ August, 2022 and the estimated ending date will be 30^th^ June, 2023.

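### The main repeated-measures ANOVA is, as written, a complete-case analysis that handles baseline as a response; the mixed model already planned as a sensitivity analysis should be primary

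*Protocol article*

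**What the plan says.** All in the Statistical methods section of the protocol article, unless another section is named:

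- **Software and main analysis.** "All statistical analyses will be conducted using SPSS (version 26.0) for Windows". For the four groups, "analysis of variances (ANOVA) with repeated measures will be performed to compare changes in actigraphy data and endogenous melatonin level between and within groups". The same sentence enters all three visits, T1, T2 and T3. The Intervention section places T1 before treatment starts, T2 five weeks in, and T3 after the 10-week programme.
- **Missing data.** The provision is a sensitivity analysis, conditional on there being missing values: "Depending on the proportion of missing data and the assumption of normality, multilevel regression or a generalized estimating equation (GEE) will also be used". No imputation is stated for the ANOVA.
- **Analysis sets.** "Both proposal analysis and intention-to-treat analysis will be carried out". The first of these presumably means per-protocol.
- **Covariates.** Baseline sedentary time and MVPA are named. The baseline value of the sleep or melatonin outcome is not. "Demographic variables (e.g. age, sex, BMI) will be adjusted if they demonstrate clinically significant prognostic effects on the outcomes", with a threshold of 0.2 on the absolute correlation or Cohen's d.
- **Follow-up tests.** "Post-hoc analyses will be performed when any significant difference both between- and within-group is found in any of the outcome variables", with Bonferroni correction.
- **Sample size calculation section.** d of about 0.9, 80% power, 5% significance, 20 per group, 25% attrition, 25 per group recruited.

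**The concern.** Three features of the main analysis work against what the trial wants to show.

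First, a classical repeated-measures ANOVA needs a full set of T1, T2 and T3 values for each child. The plan expects a quarter of the children to be lost and promises an intention-to-treat analysis, yet gives the headline result to the method that discards incomplete records. If leaving is related to burden or lack of benefit and differs by arm, the completer comparison is biased. The method that would keep these children ranks second, and its form is settled only after missingness and normality have been seen.

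Second, T1 precedes treatment and carries no treatment effect. Using it as a level of the time factor, and not as a covariate, gives up precision that a trial planned at about 80% power cannot easily spare.

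Third, demographic covariates are chosen from the observed outcome data, so the fitted model can differ from one outcome to the next.

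**Working it through.** **The plan's own figure.** For two independent means, two-sided 5%, 80% power, d = 0.9: n = 2 × (1.96 + 0.8416)² / 0.9² = 15.70 / 0.81 = 19.4, so 20 per group. This matches the plan; the noncentral t gives 20.4, so 21.

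**Completers.** 25 × (1 − 0.25) = 18.75 per arm, or 75 of 100. An analysis that needs every visit would leave out about 25 of 100 randomised children. Noncentral-t power of the planning comparison is 79% at 20 per arm, 76% at 18.75 and 88% at 25. The last is an upper bound, since no model recovers T3 values that were never observed.

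**Baseline as response or covariate.** Let r be the correlation between T1 and T3. The documents do not give it; I assume 0.3 to 0.7. In units of the outcome variance:

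- change from T1: 2(1 − r)
- T3 adjusted for T1: 1 − r²
- ratio: 2 / (1 + r)

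| r | Change | Adjusted | Ratio | Power, change | Power, adjusted |
|---|---|---|---|---|---|
| 0.3 | 1.40 | 0.91 | 1.54 | 62% | 80% |
| 0.5 | 1.00 | 0.75 | 1.33 | 76% | 87% |
| 0.7 | 0.60 | 0.51 | 1.18 | 93% | 96% |

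Power is for one pair at T3, 18.75 per arm, d = 0.9, two-sided 5%, noncentral t.

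**The test the plan names.** Comparing changes between groups over time is the group-by-time test. Simulated for one pair with 19 per arm, d = 0.9 at T3, equal correlation between visits and two-sided 5%:

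| r | Group-by-time, full effect at T2 | Group-by-time, half effect at T2 | T3 adjusted for T1 |
|---|---|---|---|
| 0.3 | 66% | 52% | 80% |
| 0.5 | 81% | 69% | 87% |
| 0.7 | 96% | 89% | 96% |

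A repeat simulation agreed within 2 points. The loss runs from 0 points (r = 0.7, full effect at T2) to 28 points (r = 0.3, half effect). These figures carry no multiplicity correction. At 0.05/6, r = 0.5 and full effect at T2, they are 58% against 64%.

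**The covariate rule under no true effect.** Take 80 children (4 × 20). For sex, the standard error of d is √(1/n₁ + 1/n₀). The sex ratio is not in the documents, so a range is shown:

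- 40 and 40: 0.2/0.224 = 0.89, P = 0.37
- 64 and 16: 0.2/0.280 = 0.72, P = 0.47
- 68 and 12: 0.2/0.313 = 0.64, P = 0.52

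For a continuous covariate such as age or BMI, |r| > 0.2 gives t = 0.2 × √(78/0.96) = 1.80, P = 0.075.

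**The case against.** The strongest reply is that the plan commits to intention-to-treat and never states that incomplete records are dropped. That is inferred from how the procedure ordinarily works. Imputation before the ANOVA could be set out in a statistical analysis plan that is not shown. A reader might infer that the main analysis cannot be intention-to-treat; the documents do not support that. What stands is that the article itself fixes the order, with ANOVA first and the partial-record models second.

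With 25% attrition expected, the multilevel or GEE analysis would almost certainly be run. The open question is therefore its form and rank, not whether it happens.

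Other stronger readings also fail:

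- **Baseline as a response breaches intention-to-treat.** It does not; it is a matter of efficiency. A model with T1 as a response and arm means constrained equal at T1 avoids the loss.
- **Including T1 dilutes the treatment effect by a third.** That applies to the between-group main effect averaged over three visits. The plan speaks of comparing changes, which is group-by-time.
- **Excluded nights shrink the completers well below 18.75.** The Primary outcome measures section excludes single nights from a seven-day recording, and a lost night is not a lost visit. No rate of invalid weeks is given.
- **The trial is open-label.** The plan says single blinded, controls receive placebo, and the analyst of sleep and melatonin is blinded. Children will know whether they jog, but actigraphy and urine are objective measures.
- **Regression to the mean will open the post-hoc gate.** Read literally, the gate also needs a between-group difference, which regression to the mean does not create under randomisation.

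Finally, a null covariate costs about one degree of freedom and does not materially bias a randomised contrast, so the covariate rule is a matter of discipline and not of validity.

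**Conclusion.** The point holds in this form: the stated main analysis is, as written, complete-case and sits badly with the intention-to-treat statement. About 25 of 100 children are at risk of being left out at the plan's own attrition rate, and T1 is used inefficiently.

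The completer count rests only on the plan's figures and the standard behaviour of the procedure. The efficiency loss rests on an assumed correlation and an assumed time course. It is substantial if the correlation is low or the effect builds after T2, and negligible at r = 0.7 with the full effect at T2. The covariate rule is a lesser matter, most visible for sex. Whether drop-out would bias the result, and in which direction, cannot be judged from the documents.

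**What to change.** Make one linear mixed model the primary analysis, in all randomised children as randomised:

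- T2 and T3 as outcomes, the T1 value of the same outcome as covariate, with arm, time and arm-by-time. Alternatively, keep T1 as a response with arm means constrained equal at T1; this also retains children who leave before T2, whom the covariate version drops.
- Base conclusions on planned between-arm contrasts at T3.
- Choose age, sex and BMI as covariates in advance, the same for every outcome, and drop the 0.2 rule.
- Keep the repeated-measures ANOVA and the per-protocol analysis as sensitivity analyses.

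The cost is wording: multilevel regression is already in the plan and available in the named software. The downsides are reliance on missing-at-random, which would fail if leaving depends on unobserved burden or benefit, and a few degrees of freedom for the fixed covariates.

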Over the past decade, a significant body of research has investigated the effects of physical exercise on sleep and the results generally supported the positive impact of physical exercise on sleep (see Kelley et al. [12] for review). Previous studies also support the sleep benefits of physical exercise in children with ASD. For example, we have examined the impact of a basketball training intervention on sleep quality (sleep efficiency and wake after sleep onset) and cognition (inhibition control and working memory) in 40 children with ASD [13]. Research revealed a significant improvement in sleep efficiency and reduction in wake after sleep onset time in the intervention group but not in the control group [13]. Similar sleep benefits following physical exercise were also evident in a more recent study [14], where we showed that jogging intervention had significantly improved sleep efficiency and sleep duration in children with ASD. More remarkably, we also observed that the endogenous melatonin level, as reflected by the 6-sulfatoxymelatonin (aMT6s), was significantly increased within the jogging intervention group, while no change was found in the control group. Physical exercise appears to be capable of modulating the endogenous melatonin level in children with ASD, which in turns improves their sleep quality. If it is so, it is then natural to ask which intervention (i.e. physical exercise or melatonin supplement of the combination of two) is more effective in treating sleep disturbance improving the sleep quality of children with ASD. Without direct comparison, this question remained unanswered. Therefore, here we propose a new study protocol.

This study protocol has two objectives: (1) to determine which intervention is more effective in improving sleep quality in children with ASD and 2) to explain how these interventions impact on sleep via melatonin-mediated mechanism model. We hypothesise that the combination intervention (i.e. jogging and melatonin supplement) is the most effective because it may provide sufficient melatonin level to enhance sleep quality through both physical exercise and melatonin supplement.

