
#### Intervention B—Melatonin supplement group

Participants in this intervention group will undergo a 10-week melatonin supplement intervention period, where melatonin supplement (Natrol®, Chatsworth CA) will be provided 30 minutes before bedtime [19]. The prescription time (i.e. 30 minutes before bedtime) and the dosage of 3mg will be used because these are optimal for most of the participants as suggested by Malow and colleagues [19]. 1 mg and 9 mg are not suggested to ensure the effectiveness of the intervention while preventing the potential daytime sleepiness. Similar to the aforementioned intervention, adherence of the intervention will be assessed at T2.

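### The four-arm ANOVA for urinary aMT6s assumes one error variance although two arms take melatonin; pooled post-hoc tests would weaken jogging versus placebo and make melatonin versus combination too liberal

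*Protocol article*

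**What the plan says.** The Statistical methods section of the protocol article gives one primary model for sleep and for melatonin: "analysis of variances (ANOVA) with repeated measures will be performed to compare changes in actigraphy data and endogenous melatonin level between and within groups", with four groups and three time points. Post-hoc analyses follow a significant result, and "Bonferroni correction will be used to adjust the alpha levels". The general threshold is "A p-value of <0.05 will be considered statistically significant". Multilevel regression or GEE is named as a sensitivity analysis, depending on the amount of missing data and on normality. Unequal variance is not among the triggers.

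Under Primary outcome measures, melatonin level is measured by creatinine-adjusted urinary aMT6s. In the melatonin arm "the dosage of 3mg will be used", taken before bedtime, and the combination arm receives the same supplement. The jogging and placebo arms receive no melatonin. T2 falls five weeks into the ten-week intervention. T3 comes after it, and the article does not say whether dosing continues during the T3 assessment week. No dosing pause before urine collection is described.

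The Introduction reports that in an earlier jogging study endogenous melatonin, "as reflected by the 6-sulfatoxymelatonin (aMT6s), was significantly increased within the jogging intervention group". The second objective is to explain the sleep effects through melatonin.

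**The concern.** A four-group ANOVA estimates one residual variance from all arms. In the two supplement arms, aMT6s reflects each child's own production plus the metabolite of an ingested dose, which differs between children with absorption, body size and adherence. On the raw scale these arms are therefore likely to be more variable while dosing lasts.

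If the pairwise tests use the pooled error, two comparisons go wrong in opposite directions:

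- **Jogging versus placebo.** This is the one melatonin contrast free of ingested melatonin. Its standard error is inflated by noise from the other two arms, so a real rise may be missed.
- **Melatonin versus combination.** This bears on the hypothesis that combining the interventions supplies more melatonin. Its standard error is too small, so chance differences are declared too often.

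The requirement of a significant overall test gives no protection. If the supplement itself raises aMT6s, the overall test is significant for that reason and the pairwise tests go ahead.

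**Working it through.** **Inputs from the protocol article.** Sample size calculation: "A sample of 20 participants per group is computed by G*power software". The targets there are 80% power and a 5% level, for an effect "corresponding to a Cohen’s *d* of about 0.9". That effect is stated for sleep outcomes.

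**Assumptions.**
- Two-sided tests.
- A jogging effect of 0.9 SD on aMT6s, borrowed because none is given.
- A Bonferroni family of six pairs, so 0.05/6 = 0.0083.
- SD ratio k of dosed to undosed arms. No aMT6s SD is given.

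**Plan's own figure.** n = 2(1.96 + 0.8416)²/0.9² = 19.4, so 20 per group. The stated 20 is reproduced. Exact power of a two-sample t test at n = 20 is 79.2%.

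**Formulas.** With SDs 1, 1, k, k and equal arms, the pooled variance is (1 + 1 + k² + k²)/4 = (1 + k²)/2.
- Jogging versus placebo: pooled/true variance R = (1 + k²)/2. Expected unscaled statistic: 0.9√(20/2) = 2.846. Approximate power: Φ(2.846 − 1.992√R), where 1.992 is the 5% critical value on 76 df.
- Melatonin versus combination: pooled/true variance R′ = (1 + k²)/(2k²). Approximate type I error: 2[1 − Φ(z√R′)]. As k grows, R′ tends to 1/2.

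By hand at k = 2: R = 2.5, power ≈ Φ(2.846 − 3.149) = 38%; R′ = 0.625, type I error ≈ 2[1 − Φ(1.550)] = 12.1%.

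**Simulation.** Follow-up values, 20 per arm, 40,000 trials per k, pooled error on 76 df:

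| k | R | Jogging–placebo power, 5% | Same, 0.83% | Melatonin–combination type I error, nominal 5% | Same, nominal 0.83% |
|---|---|---|---|---|---|
| 1 | 1 | 80% | 56% | 5.1% | 0.9% |
| 1.5 | 1.625 | 62% | 29% | 9.5% | 2.4% |
| 2 | 2.5 | 39% | 9% | 11.9% | 3.7% |
| 3 | 5 | 7.5% | 0.3% | 14.5% | 5.1% |
| limit | – | 0% | 0% | 16.6% | 6.2% |

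**Change from T1.** The plan compares changes, and no arm is dosed at T1. With an assumed within-child correlation of 0.5, the change-score variance is 1 in undosed arms and 1 + k² − k in dosed arms, so R = (2 + k² − k)/2: 2 at k = 2 and 4 at k = 3. Simulated power at 5% is 51% and 15%; melatonin–combination type I error at nominal 5% is 10.7% and 13.8%.

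**Dosing stopped before T3.** Averaging over T1–T3 with SDs 1, 5, 1 and correlation 0.5, the variance of the sum is 27 + 11 = 38, against 6 in an undosed arm. The SD ratio is √(38/6) ≈ 2.5. A ratio of 5 at T2 alone is diluted but still present in a time-averaged error term, while T3 taken alone may be unaffected.

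**Alternatives.** Separate-variance (Welch) tests keep jogging–placebo power at 79% (53% at 0.83%) and melatonin–combination error at about 5% (0.8%) for every k. A log scale with equal coefficients of variation gives about 80% (56%) and 5% (0.8%).

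**The case against.** A reader might infer that the jogging-versus-placebo melatonin test loses nearly all its power. The documents do not support that: it needs k of about 3 or more, and no aMT6s SD or effect is given. At k between 1.5 and 2 the loss is partial. Nor should the whole shortfall from 80% be charged to pooling, because Bonferroni over six pairs alone leaves 53–56% with equal variances.

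A reader might also quote a false-positive rate near 16% for the planned test. The plan applies Bonferroni, and for six pairs the contrast's error cannot exceed about 6.2%. That is well above its nominal 0.83% but only slightly above 5%.

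The article names neither the post-hoc test nor the scale. Its Bonferroni wording would fit separate two-arm tests at a reduced alpha, and a transformation may sit in an analysis plan that is not shown. This stands, and it makes the figures conditional on pooled post-hoc error. It does not remove the point, because the article does fix the primary model and the triggers for adding another, and neither addresses unequal variance.

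The fallback deserves more credit than it might first get. With 25% attrition assumed, missing data are expected, and GEE with its usual robust variance does not need equal variances. But it remains a sensitivity analysis, and multilevel regression is the named alternative to it.

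Finally, the mechanism objective is also addressed by a bootstrapped mediation analysis that does not rest on the four-arm ANOVA error. So it does not follow that a real melatonin rise would go unreported altogether.

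**Conclusion.** The point holds in conditional form. The stated model for aMT6s assumes a common variance that the design makes unlikely while two arms are being dosed. For any k above 1, pooled post-hoc tests are conservative for jogging versus placebo and liberal for melatonin versus combination. With 20 per arm and a borrowed 0.9 SD effect, modest ratios of 1.5 to 2 cost 18 to 41 percentage points of power at 5% on follow-up values; the cost is smaller on change scores.

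This is clear at T2. At T3 it depends on whether dosing continues in the assessment week. The sleep outcomes are not touched by this argument. It is worth correcting because aMT6s is listed as a primary outcome and the remedy is nearly free.

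**What to change.** For aMT6s, analyse log values adjusted for T1 with arm-specific residual variances, either by a mixed model with variance by arm or by separate-variance contrasts. Test jogging versus placebo using only those two arms' variance. Keep the arm-specific variances even on the log scale, since logs equalise the spread only if variation is proportional to level. State the post-hoc test and the Bonferroni family, and record whether T3 urine is collected on or off supplement, so that the reach of the point at T3 is clear.

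This takes a sentence or two in the analysis section and no extra data. The downsides are small: effects are reported as ratios, and denominator degrees of freedom fall slightly. If variances turn out equal, power at 5% is 79% instead of 80%, or 53% instead of 56% at 0.83%.
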